## Methods

### Study aims and hypotheses

The aims of this study are to evaluate the impact of *Navigate* for men with low-risk prostate cancer and their partners on uptake of AS as a first-line management option; men’s preparedness for decision-making; men’s decisional conflict, regret and satisfaction; the quality of men’s illness communication; and men’s prostate cancer-specific quality of life. The secondary aims are to estimate study arm differences in men’s anxiety; explore the impact of *Navigate* on partner’s decisional conflict, regret and satisfaction, and quality of illness communication; assess the healthcare cost impact and cost-effectiveness of *Navigate* (economic sub-study); and determine the specific patterns of use of *Navigate* (web analytic sub-study).

Specific hypotheses are that a higher proportion of men randomised to *Navigate* will select AS as a first-line management option when compared with men randomised to the control group, and men randomised to *Navigate* will feel better prepared for decision-making, experience lower levels of decisional conflict and regret and higher levels of decisional satisfaction and report better quality of illness communication and better prostate cancer-specific quality of life when compared to men randomised to the control group.

Research questions, rather than hypotheses, were developed for secondary aims, since no specific predictions were made. Research questions relevant to the main study include:

*Do men randomised to Navigate report higher or lower levels of anxiety than men in the control group?*

*Do the partners of men randomised to Navigate experience lower levels of decisional conflict and regret, and higher levels of decisional satisfaction when compared with the partners of men randomised to the control group?*

The research question for the economic sub-study is:

*What is the cost-effectiveness of the decision-aid intervention compared with usual care for men newly diagnosed with prostate cancer?*

The research questions for the web analytic study include:

*What are the general patterns of use of the website; are there any identifiable areas for improvement from a user experience perspective?*

*Do men diagnosed with prostate cancer use the website differently compared with partners of these men?*

*What are the patterns of use across individuals relating to the values clarification exercise?*

*Do patterns of use relate to the primary and secondary outcome variables?*

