### Main study measures

#### Demographic and clinical information

Demographic information collected from patients and partners includes age (in years), marital status, postcode, highest education level, occupation and ethnic origin.

Clinical information (Gleason score and PSA) is obtained from the referring site or the referring clinician or collected via a medical record audit.

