### Secondary outcomes

*Preparedness for decision-making* is assessed at follow-up 1 with the preparedness for decision-making scale (PrepDM). The PrepDM total scale measures the perceived usefulness of the decision aid in preparing the patient to communicate with his doctor(s) to make a health decision and has shown acceptable internal consistency (Cronbach’s *α* = 0.92 to 0.96), and Item Response Theory analyses demonstrated that all ten scale items function well [38].

*Decisional conflict* is assessed at follow-up 1 with the 16-item Decisional Conflict Scale (DCS). The DCS measures patients’ perceptions of uncertainty, being uninformed and unsupported and having unclear values in decision making. The DCS is suitable for use with cancer patients and has shown acceptable internal consistency (Cronbach’s *α* = 0.78–0.92), test-retest reliability (*r* = 0.81) and responsiveness (longitudinal validity) [39].

*Decisional satisfaction* is assessed at follow-up 2 and, for patients only, follow-up 3 with the 6-item Satisfaction with Decision (SWD) measure. The SWD has shown acceptable internal consistency (Cronbach’s *α* = 0.86), discriminant validity and responsiveness [31, 40].

*Decisional regret* is assessed at follow-up 2 and, for patients only, follow-up 3 with the 5-item Decisional Regret Scale (DRS). The DRS has shown acceptable internal consistency (Cronbach’s *α* = 0.81–0.92) and convergent validity with related measures (*r* = 0.31–0.60) and responsiveness [31].

The quality of men’s and partners’ *illness communication* is assessed at baseline and follow-up 1 with the 4-item Couples’ Illness Communication Scale (CICS). The CICS was adapted for use in prostate cancer populations. The original scale has shown acceptable internal consistency (Cronbach’s *α* = 0.80) and convergent validity with other measures of dyadic adjustment [41].

*Anxiety* is assessed at baseline and follow-up 1 with the 7-item PROMIS Emotional distress-Anxiety 7a short-form. The Anxiety 7a is a standardised, valid and precise measure specifically developed for use in clinical oncology research [42].

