### Outcome analysis

The primary analysis will follow the intention-to-treat principle and all study participants will be analysed as part of the study arm to which they were randomised in all outcome analysis. Missing data will be imputed using multiple imputation, redrawing 50 samples. Pearson’s chi squared test will be used to analyse study arm differences in the primary outcome. Linear regression will be used to analyse study arm differences for preparedness for decision-making at follow-up 1, illness communication at follow-up 1 and anxiety at follow-up. Each model will be adjusted for baseline and group assignment. Decisional conflict (follow-up 1), satisfaction (follow-ups 2 and 3) and regret (follow-ups 2 and 3) will be analysed using linear regression with group assignment as the independent covariate (equivalent to a test). The effect between groups and significance will be assessed using the beta-coefficient and *p* value corresponding to the group assignment term. Finally, prostate cancer-specific quality of life will be analysed with a random effects mixed model. The independent variables will be group assignment, time (coded 0/1) and the interaction term group assignment BY time. The effect and between groups and significance will be assessed using the beta-coefficient and *p* value corresponding to the interaction term. All results will be presented with 95% confidence intervals and a *p* value less than 0.05 (two-sided) will be deemed to be statistically significant.

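### The group-only models for men's decisional conflict, satisfaction and regret are valid but forgo a modest gain in precision from baseline anxiety, age, education and recruitment site

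*Protocol article*

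**What the plan says.** Under Study aims and hypotheses, the article predicts that men given the decision aid will "experience lower levels of decisional conflict and regret and higher levels of decisional satisfaction" than controls. Three of the named hypotheses therefore concern decisional outcomes. With satisfaction and regret each measured twice, they give five outcome-by-time comparisons.

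Under Outcome analysis, these outcomes "will be analysed using linear regression with group assignment as the independent covariate (equivalent to a test". No other term is listed. For the preceding group of outcomes (preparedness, illness communication and anxiety) the same paragraph says: "Each model will be adjusted for baseline and group assignment".

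Under Secondary outcomes, decisional conflict "is assessed at follow-up 1 with the 16-item Decisional Conflict Scale (DCS", and satisfaction and regret are first measured at follow-up 2. None of the three has a baseline score. Anxiety, by contrast, "is assessed at baseline and follow-up 1 with the 7-item PROMIS Emotional distress-Anxiety 7a short-form". Demographic and clinical information lists "age (in years), marital status, postcode, highest education level, occupation and ethnic origin".

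Under Trial design and randomisation, men are randomised after the baseline measures are complete, one-to-one and stratified by recruitment site. The same section has statisticians unblinded before the flow diagram and outcome analysis are prepared.

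**The concern.** The plan accepts baseline adjustment for some continuous outcomes but not for these three, apparently because they have no baseline score of their own. A covariate need not be the same scale as the outcome to be useful; it needs only to be measured before randomisation and to predict the outcome. Baseline anxiety is a natural candidate. The Background (Treatment decision making in LRPC) describes anxiety among men contemplating surveillance, and the Discussion lists anxiety, distress and decisional regret together. Site is a candidate because the design stratifies on it. If outcomes differ between sites, leaving site out keeps that variation in the residual, and the standard error is larger than it need be.

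What is at stake is the width of the confidence intervals on three named hypotheses. The trial is sized for the binary primary outcome only, and the article gives no target difference or power for the decisional scales.

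**Working it through.** **1. The plan's own figure.** Inputs from Sample size: 65% v 80%, two-sided α = 0.05, power 80%.

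n per arm = (1.960 + 0.842)² × [0.65 × 0.35 + 0.80 × 0.20] / 0.15² = 7.849 × 0.3875 / 0.0225 = 135.2, so 136 per arm and 272 in all. Allowing for 10% attrition, 136 / 0.9 = 151.1, so 152 per arm and 304 in all. Both stated totals reproduce. They concern active-surveillance uptake and are unaffected by this point.

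**2. Group-only model at 136 per arm.** In SD units, SE = √(2/136) = 0.1213.
- Detectable difference at 80% power = 2.802 × 0.1213 = 0.340 SD.
- Power at 0.30 SD = Φ(0.30/0.1213 − 1.960) = Φ(0.514) = 69.6%. The 0.30 SD is illustrative; the article gives no target.

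**3. Adjusted model.** If the covariates explain a share R² of the within-arm outcome variance, SE = √(2(1 − R²)/136). The article gives no R², so a range is assumed.

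| Assumed R² | Detectable difference (SD) | Power at 0.30 SD | Equivalent n per arm, 136/(1 − R²) |
|---|---|---|---|
| 0 | 0.340 | 69.6% | 136 |
| 0.05 | 0.331 | 71.8% | 143 |
| 0.10 | 0.322 | 74.1% | 151 |
| 0.16 | 0.311 | 77.0% | 162 |

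**4. Cost in degrees of freedom.** With k covariate terms and N = 272, the variance is multiplied by (1 − R²)(N − 3)/(N − 3 − k). This equals 1 at R² = k/(N − 3) = k/269.
- k = 4 (anxiety, age, education as one term, one site contrast): 4/269 = 0.015.
- k = 10: 10/269 = 0.037. This counts three terms for anxiety, age and education, and seven for site. The seven site terms assume that the seven named hospitals and self-referral make eight strata; the article does not say how self-referred men are stratified.

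At k = 10 the table's end points shrink:
- R² = 0.05: variance factor 0.95 × 269/259 = 0.987, detectable difference 0.338 SD, power at 0.30 SD about 70%.
- R² = 0.16: variance factor 0.84 × 269/259 = 0.872, detectable difference 0.317 SD, power about 75%.

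If R² were exactly zero, the factor 269/259 = 1.039 would widen the interval by about 2%.

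**5. Timing of the covariates.** Anxiety is stated to be measured at baseline, and baseline measures precede randomisation. For age and education no collection time is given. Baseline is inferred from the list of demographics and from the plan under Statistical analysis to compare baseline characteristics of drop-outs and continuing participants.

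**The case against.** The strongest reply is that nothing here is wrong. Randomisation makes the group-only comparison unbiased and its test valid. The plan also has a logic: illness communication and anxiety have baseline scores and are adjusted, while the three decisional scales have none and are not. Satisfaction and regret about a decision cannot be measured in men who have yet to make it. The choice of further covariates is often left to an analysis plan, and nothing forbids a supplementary adjusted analysis. No figure in the article shows that baseline anxiety, age, education or site predicts these outcomes one to six months later.

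Most of this stands. It makes the point one of efficiency and limits its size. It does not remove it, because the article states the model rather than leaving it open.

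A reader might infer more from the text in three ways that it does not support.
- **That the tests are biased or the hypotheses invalidly tested.** They are not; only precision is affected.
- **That the conflict scale should have been given at baseline, with a large gain.** The quoted r = 0.81 is test-retest reliability. It is not the correlation between an undecided man's score at entry and his score a month later, after an intervention meant to change it. Recruitment opened in May 2017 and was expected to end in December 2020, and the current protocol version is dated March 2020, so most men would have no such score.
- **That every baseline scale should enter the model.** The illness communication measure is a couples' scale and nominating a partner is optional, so it may not apply to every man.

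**Conclusion.** The point holds as a modest missed gain in precision, not as an error. For men's decisional conflict, satisfaction and regret the article fixes a model with group alone, although baseline anxiety and the stratification factor are available, and age and education very probably are too.

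The gain runs from nothing to modest. Before the cost in degrees of freedom, an assumed R² of 5–16% gives a detectable difference of 0.331–0.311 SD instead of 0.340 SD; with many site terms the lower end of that gain nearly disappears. A reader might take a loss of precision as established, but the documents cannot show that, because they give no R².

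The figures assume 136 evaluable men per arm at each time point and a common within-arm variance. They take no account of the planned multiple imputation.

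**What to change.** For men's decisional conflict (follow-up 1), satisfaction and regret (follow-ups 2 and 3), replace the group-only model with a pre-specified linear regression on group, recruitment site, baseline PROMIS anxiety, age and education. Keep the group coefficient, with its 95% confidence interval, as the effect estimate; it is still a difference in means. Report the group-only result as a sensitivity analysis.

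State in advance how education is coded, how small sites are combined and where self-referred men are placed, so that the number of terms stays small. Confirm that age and education were recorded before randomisation. Leave out the couples' illness communication score, and do not add a baseline conflict questionnaire.

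Record the change before statisticians are unblinded, so that the covariates cannot be chosen in the light of the results. The cost is a change of analysis wording and a few degrees of freedom. No new data are needed, and the sample size does not change.

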### Trial design and randomisation

This study will use a parallel group, prospective randomised controlled trial (RCT) with one baseline and three post-baseline assessments (i.e. follow-ups 1, 2 and 3), along with economic and web analytics substudies. In this study, ‘partner’ refers to the support person nominated by the patient. Both patients and their partners (if one is nominated) will be invited to participate. Following informed consent and completion of baseline study measures, participating patients and their partners will be randomly assigned to *Navigate* or the usual care arm with a one-to-one allocation, stratified by recruitment site. Randomisation will be undertaken remotely and independently by the trial coordinator using a purpose-built Microsoft Access randomisation database. After a participant (patient/partner) has been enrolled and completed baseline measures, the trial coordinator uses the randomisation database to assign the participant to the intervention or usual care arm and informs them via email of the experimental allocation. Post-baseline assessments will occur approximately 1, 3 and 6 months after consent. Participants will be informed of their allocation after completing baseline questionnaires. Researchers involved in data collection will be blinded to group allocation. Statisticians will be unblinded to allocation before preparation of the participant flow diagram and outcome analysis. Ethical approval was received from the Peter MacCallum Cancer Centre Human Research Ethics Committee (HREC16 PMCC114). Figure 1 displays the enrolment, group allocation, intervention and assessment schedule.

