*Prostate cancer-specific quality of life* is assessed at baseline and every follow-up with the 26-item Expanded Prostate Cancer Index Composite short-form (EPIC-26). The EPIC-26 comprises four subscales: urinary, bowel, sexual and hormonal. The hormonal subscale is not relevant in this context, so will not be administered. Subscales have shown acceptable internal consistency (all Cronbach’s *α* > 0.70), test-retest reliability (all *r* > 0.69) and responsiveness when used independently [43].

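### The EPIC-26 mixed model compares raw change from a pre-randomisation baseline; conditioning on baseline is never less precise and usually more so

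*Protocol article*

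**What the plan says.** Under Secondary outcomes, the protocol article says that prostate cancer-specific quality of life "is assessed at baseline and every follow-up with the 26-item Expanded Prostate Cancer Index Composite short-form (EPIC-26". Trial design and randomisation gives the schedule, "Post-baseline assessments will occur approximately 1, 3 and 6 months after consent", and the order of events: "Following informed consent and completion of baseline study measures, participating patients and their partners will be randomly assigned". The baseline score therefore precedes allocation.

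Under Outcome analysis, "prostate cancer-specific quality of life will be analysed with a random effects mixed model". The fixed effects are listed in full: "The independent variables will be group assignment, time (coded 0/1) and the interaction term group assignment BY time". The test is also fixed: "significance will be assessed using the beta-coefficient and *p* value corresponding to the interaction term". No baseline covariate is named and no common baseline mean is imposed.

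The same paragraph handles other outcomes differently. After naming the linear regressions, which include illness communication and anxiety (both also measured at baseline), it says "Each model will be adjusted for baseline and group assignment". That sentence refers to those regressions, not to the EPIC-26 model that comes later.

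**The concern.** Randomisation makes the expected arm difference at baseline zero, so any observed difference is chance. A model with baseline as an outcome row and a group main effect estimates that difference freely. The interaction then subtracts the whole chance imbalance from the follow-up difference, although only the part that predicts follow-up should be removed.

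What is at stake is precision. Better prostate cancer-specific quality of life is one of the specific hypotheses under Study aims and hypotheses, and it is tested at two-sided 0.05. The sample size was set for uptake of active surveillance alone, so EPIC-26 has no planned power in reserve. The terms and the tested coefficient are written out, so this is a stated choice and not a detail left to an analysis plan that is not shown.

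**Working it through.** **The plan's own figure.** The only sample size stated is for the primary outcome. With 65% vs 80%, two-sided 0.05 and 80% power, the unpooled normal approximation gives (1.960 + 0.842)² × (0.65×0.35 + 0.80×0.20) / 0.15² = 135.2, so 136 per arm and 272 in total. Allowing for 10% attrition, 136/0.9 = 151.1, so 152 per arm and 304 in total. Both figures reproduce. There is no power, SD or target effect for EPIC-26 to reproduce.

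**Inputs**
- From the protocol: 136 men per arm, two-sided 0.05, one baseline and three follow-ups.
- Assumed: time 0 is baseline; data are complete; all visits share a common correlation ρ; baseline SD is 1 and follow-up SD is s.
- The only related figure given is "test-retest reliability (all *r* > 0.69) and responsiveness when used independently". That is a reliability, not a correlation over 1 to 6 months, so ρ is varied from 0.5 to 0.9.

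**Per-man variances with k follow-ups averaged**
- Mean of follow-ups: V = s²(1 + (k−1)ρ)/k
- Planned (mean follow-up minus baseline): V + 1 − 2ρs
- Conditioning on baseline: V − (ρs)²
- Planned minus adjusted: (1 − ρs)²

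The last line settles the direction. The excess is a square, so it is never negative, and it is zero only when the slope ρs equals 1.

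**Equal SDs (s = 1).** Choose the effect that the adjusted model detects with 80% power. Planned power is then Φ(2.802/√ratio − 1.960), where ratio is planned variance over adjusted variance.

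| ρ | k | Planned | Adjusted | Ratio | Planned power |
|---|---|---|---|---|---|
| 0.5 | 1 | 1.000 | 0.750 | 1.33 | 68% |
| 0.69 | 1 | 0.620 | 0.524 | 1.18 | 73% |
| 0.8 | 1 | 0.400 | 0.360 | 1.11 | 76% |
| 0.9 | 1 | 0.200 | 0.190 | 1.05 | 78% |
| 0.5 | 3 | 0.667 | 0.417 | 1.60 | 60% |
| 0.69 | 3 | 0.413 | 0.317 | 1.30 | 69% |
| 0.8 | 3 | 0.267 | 0.227 | 1.18 | 73% |
| 0.9 | 3 | 0.133 | 0.123 | 1.08 | 77% |

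At ρ = 0.69 and k = 3, the effect detectable with 80% power is 2.802 × √(2 × 0.413/136) = 0.218 SD as planned and 2.802 × √(2 × 0.317/136) = 0.191 SD with adjustment.

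**Unequal SDs, ρ = 0.69**

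| Follow-up SD / baseline SD | Slope ρs | Planned power, k = 1 | Planned power, k = 3 |
|---|---|---|---|
| 1.0 | 0.69 | 73.1% | 68.9% |
| 1.1 | 0.76 | 76.5% | 74.2% |
| 1.2 | 0.83 | 78.5% | 77.5% |
| 1.3 | 0.90 | 79.5% | 79.2% |

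**Confirmation.** Generalised least squares for the four-visit model gives the change-score variance when the group main effect is kept (0.667 at ρ = 0.5, 0.400 at ρ = 0.7). It gives the adjusted variance when that term is dropped (0.417, 0.310). In 4,000 simulated trials with three pooled follow-ups, both estimators were unbiased, and power for change against adjustment was 60% vs 80% at ρ = 0.5 and 68% vs 80% at ρ = 0.7.

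**The case against.** The best defence is that a group-by-time term in a mixed model is a standard and valid analysis of a randomised trial, and that nothing the protocol claims about EPIC-26 is numerically wrong. Both parts stand. A reader might infer that the planned estimate is biased, because an arm that starts low by chance tends to appear to improve. That holds only conditionally on an observed imbalance. With 136 per arm, a one-standard-error imbalance is √(2/136) = 0.12 SD, which shifts the estimate by about (1 − 0.69) × 0.12 = 0.04 SD and averages to zero over randomisations.

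A reader might also infer that change scores lose precision at every correlation below 1. That is true only with equal SDs. Men join before choosing a treatment and then divide between surveillance and curative treatment, and the Background reports worse urinary and sexual outcomes after prostatectomy. A wider spread at follow-up is therefore plausible, and it would bring the slope nearer to 1 at the correlations considered near 0.69. The protocol gives no SDs, so this cannot be settled; a narrower spread would enlarge the loss.

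Nor does the document support quoting a 20-point power loss as the expected cost. That figure needs an assumed ρ of 0.5 and all three follow-ups pooled as time 1.

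Finally, the protocol does not say that 0 means baseline or how four assessments map to 0/1. That ambiguity is a separate matter. With visit as a categorical factor, a free group main effect at baseline would still make each visit contrast a change-score comparison. What remains after these objections is the direction of the loss and the absence of any stated reason for accepting it.

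**Conclusion.** Reading time 0 as baseline, the concern holds as a point about efficiency, not validity. The planned interaction is never more precise than conditioning on baseline (apart from the negligible cost of estimating one slope), and is less precise unless the slope is exactly 1. The size is uncertain. With equal SDs and ρ of 0.69, the loss is about 7 points of power with one follow-up and 11 with three pooled. With equal SDs and ρ of 0.9 it is 2 to 3 points, and with ρ of 0.69 and follow-up SD 20% larger it is 1.5 to 2.5. All these figures assume complete data, a common correlation and 136 men per arm. The change is worth making because it costs almost nothing, but the outcome is secondary.

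**What to change.** Replace the EPIC-26 model sentence with one of two equivalent-purpose specifications:

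- Model the follow-up scores only, with group, visit and each man's baseline subscale score as a covariate, as the same paragraph already does for illness communication and anxiety.
- Keep baseline as an outcome row but drop the group main effect, leaving time and group-by-time, so that both arms share one baseline mean. The covariance structure should let baseline and follow-up variances differ; otherwise the slope is not estimated freely.

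In either case, read the arm effect from the follow-up group term or terms, and state what time 0 and 1 denote.

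The cost is one sentence and one changed term in the Stata model. It needs no new data and no more patients. It should be settled before the statisticians are unblinded to allocation.

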## Background

Prostate cancer is one of the most commonly diagnosed cancers on a global scale, with incidence rates of 1.1 million during 2012 alone [1]. The vast majority of cases are detected within high-income regions such as Australia, New Zealand, Northern America and Western and Northern Europe. The high incidence rates have been attributed to the widespread use of prostate-specific antigen (PSA) testing [2]. Fortunately, the majority of prostate cancers are localised at the time of diagnosis [3]. Although early detection strategies can reduce the risk of disease progression, they can also result in overtreatment, particularly in men diagnosed with low-risk prostate cancer (LRPC).

Men diagnosed with LRPC may be offered curative treatment options, including radical prostatectomy (RP), radiotherapy (RT) and brachytherapy (BT), or may be managed with routine monitoring called active surveillance (AS). It is estimated that up to 50% of all prostate cancer cases do not require curative treatment up to 12 years post-diagnosis [4]. Indeed, evidence suggests that there is no survival benefit in providing curative treatments for LRPC at least up to 10 years after diagnosis [5, 6]. Moreover, these curative treatment options are commonly associated with both short- and long-term side effects such as erectile dysfunction, urinary and bowel incontinence and reduced quality of life [6–8]. This underscores the importance of patient involvement in decision-making regarding the commencement of curative treatment during early-stage disease [9].

AS is now recommended as a preferred management strategy for LRPC [9–13], although rates of AS uptake vary widely around the world [14]. AS is a proactive approach which aims to delay or avoid radical treatments through close monitoring of both the patient and the tumour [15]. AS is now widely accepted as an effective management strategy for LRPC, and clinicians are encouraged to offer AS to eligible patients [9, 13, 16, 17]. AS has also been shown to be the least costly option for LRPC and increased uptake of AS would lead to substantial cost-savings to the health system [18].

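### EPIC-26 is measured on four occasions but modelled with a binary time variable and one interaction, so the contrast that tests the quality-of-life hypothesis is undefined

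*Protocol article*

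**What the plan says.** The section Trial design and randomisation sets out "one baseline and three post-baseline assessments (i.e. follow-ups 1, 2 and 3", and adds: "Post-baseline assessments will occur approximately 1, 3 and 6 months after consent". Under Secondary outcomes, prostate cancer-specific quality of life "is assessed at baseline and every follow-up with the 26-item Expanded Prostate Cancer Index Composite short-form (EPIC-26". That makes four measurement occasions.

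Under Outcome analysis, "prostate cancer-specific quality of life will be analysed with a random effects mixed model". Its terms are given as: "The independent variables will be group assignment, time (coded 0/1) and the interaction term group assignment BY time". For the test, "significance will be assessed using the beta-coefficient and *p* value corresponding to the interaction term". The section does not say which visits take the value 0 and which take 1.

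Quality of life is one of the specific hypotheses. Under Study aims and hypotheses, men given *Navigate* are expected to "report better quality of illness communication and better prostate cancer-specific quality of life when compared to men randomised to the control group". No visit is named there either. By contrast, Outcome analysis does name the visits for decisional conflict (follow-up 1) and for satisfaction and regret (follow-ups 2 and 3).

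**The concern.** A model that leaves the means of four occasions free needs three time indicators and three group-by-time terms. The article specifies one of each. Two analysts could follow the sentence faithfully and test different quantities: one an average over all follow-ups, the other the change to a single follow-up of the analyst's choosing. The statisticians are to be unblinded before the outcome analysis (Trial design and randomisation), so it matters that this choice is fixed on paper beforehand.

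If the follow-ups are pooled, the timing of any benefit also matters. Men enter before making a treatment decision (Eligibility criteria), and their choice is recorded at follow-up 1 (Primary outcome). The Background states that "these curative treatment options are commonly associated with both short- and long-term side effects". If quality of life improves because such effects are avoided, little of the difference may exist at 1 month. A pooled coefficient would then understate the difference present later.

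**Working it through.** **Plan's own figure.** The article gives no sample size or power for EPIC-26. Its only calculation is for uptake of active surveillance (Sample size): 65% against 80%, two-sided 5%, 80% power. With unpooled variance, (1.960 + 0.842)² × (0.65 × 0.35 + 0.80 × 0.20) / 0.15² = 135.2, so 136 per arm. Then 136 / 0.9 = 151.1, so 152 per arm and 304 in total. This reproduces the stated figures and is untouched by the present point.

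**Counting terms.**
- Occasions: 1 baseline + 3 follow-ups = 4.
- Needed for free means: 3 time indicators and 3 interactions. Specified: 1 and 1.
- What fits the text: (a) baseline = 0 and all follow-ups = 1; or (b) two occasions kept and two dropped.

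**Illustration of reading (a).** The documents give no effect size, SD or correlation for EPIC-26, so these are assumptions: 136 per arm, equal correlation r between visits, unit SD, random-intercept model, complete data.

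- Pooled contrast (mean of three follow-ups minus baseline): variance = (1 + 2r)/3 + 1 − 2r = (4/3)(1 − r).
- 6-month change from baseline: variance = 2(1 − r).
- SE = √(2 × variance / 136); power = Φ(effect/SE − 1.96).

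At r = 0.6:
- Pooled: variance 0.533, SE 0.0886.
- 6-month change: variance 0.800, SE 0.1085.

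With effects 0 / 0.15 / 0.30 SD at 1 / 3 / 6 months:
- Pooled effect = (0 + 0.15 + 0.30)/3 = 0.15; 0.15/0.0886 = 1.69; power 0.40.
- 6-month effect = 0.30; 0.30/0.1085 = 2.77; power 0.79.

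Other patterns at r = 0.6:

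| Effect at 1 / 3 / 6 months (SD) | Pooled estimate (SD) | Pooled power | 6-month change power |
|---|---|---|---|
| 0.05 / 0.15 / 0.30 | 0.17 | 0.47 | 0.79 |
| 0 / 0.15 / 0.30 | 0.15 | 0.40 | 0.79 |
| 0 / 0 / 0.30 | 0.10 | 0.20 | 0.79 |
| 0.30 / 0.30 / 0.30 | 0.30 | 0.92 | 0.79 |
| 0 / 0.30 / 0.15 | 0.15 | 0.40 | 0.28 |

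For the 0 / 0.15 / 0.30 pattern with r from 0.5 to 0.7, pooled power runs from 0.33 to 0.50 and 6-month change power from 0.70 to 0.89. Both columns use unadjusted change from baseline, so the comparison reflects only how time is handled. Adjusting for baseline would raise the 6-month figure (to about 0.87 at r = 0.6), but that gain has nothing to do with time coding.

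**Reading (b).** If baseline and one follow-up are kept, the coefficient is the change contrast for that visit. Nothing is diluted, but two visits of collected data go unused and the text does not say which visit survives.

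**The case against.** The strongest reply is that a pooled before-and-after contrast is a legitimate choice. The hypothesis names no visit, so an average difference over follow-up answers it directly. Pooling also wins on power if the effect is constant or peaks at 3 months, as the table shows. This stands. It rules out several stronger conclusions that a reader might infer:

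- *That the hypothesis is certainly tested on a diluted contrast.* Dilution needs both pooling and an effect that differs by visit. The documents establish neither. The Background mentions short-term as well as long-term side effects and does not say that the difference grows steadily to 6 months.
- *That the coefficient is biased towards no effect.* An average over follow-ups is a different target, estimated without bias for that average. A time trend shared by both arms costs precision but does not bias the arm comparison when visits are balanced.
- *That 6 months is the right deciding visit.* The article never says so.

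A second reply is that 0/1 may be shorthand for a set of dummy indicators. That does not fit the singular interaction term, coefficient and p value. With three dummies there would be three of each and no rule for choosing among them.

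A third is that this is a condensed article and visit coding belongs in an analysis plan. That would answer a complaint about silence. Here, however, the article states the coding, the terms and the tested coefficient, and what it states does not match its own assessment schedule.

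**Conclusion.** The point holds as a mismatch between the stated model and the design: four occasions, a two-level time variable, and one tested coefficient whose meaning depends on an unstated choice. The contrast that would decide the quality-of-life hypothesis is therefore undefined.

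The size of the consequence is conditional. If follow-ups are pooled and the benefit emerges after month 1, which is plausible here, the estimate is about 33% to 56% of the 6-month effect in the three late-emerging patterns shown, and power falls from about 79% to between 20% and 47%. If the effect is constant, pooling loses nothing and gains power. All these figures rest on an assumed 6-month effect of 0.30 SD, r = 0.6 and 136 men per arm with complete data.

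The outcome is secondary. The primary outcome, its chi-squared test and the sample size are unaffected.

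**What to change.** In Outcome analysis, replace the 0/1 time variable with time as a four-level categorical factor (baseline, 1, 3 and 6 months) and include the group-by-time terms. Alternatively, model the three follow-ups with baseline EPIC-26 as a covariate.

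Then name, before analysis, one contrast for each administered subscale on which significance is judged. It may be the arm difference at a stated visit, such as 6 months, or an explicitly declared average over the follow-ups. Either is defensible if declared. Report the remaining visit-specific contrasts as descriptive.

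The cost is about one sentence of text and no new data. With the four-level factor, the model uses three interaction terms instead of one, that is, two more interaction degrees of freedom.
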